Appendix 1: Study design [31](#__RefHeading___Toc58666128)

Appendix 2: Sample Case Record Form [32](#__RefHeading___Toc58666129)

Appendix 3: Patient Information Sheet [42](#__RefHeading___Toc58666140)

# Introduction

The overall aim of this study is to assess the tolerability and anti-cancer properties of oral artesunate (an established antimalarial agent) for colorectal cancer (a new indication).

## Background

Colorectal cancer (CRC) is the third commonest cancer in industrialised countries, with over 1 million individuals diagnosed each year [1]. Early diagnosis and surgical treatment can be curative. However, up to half of the patients with CRC present with advanced stages of disease and require adjuvant therapy, where the chances of cure are correspondingly diminished.

Current adjuvant therapies now include expensive biologically targeted agents such as the humanised monoclonal anti-VEGF antibody bevacizumab given with combination anti-cancer chemotherapeutic regimens that contain 5-fluorouracil with oxaliplatin (FOLFOX) or with irenotecan (FOLFIRI) [2]. Despite demonstrated survival benefits with bevacizumab used in combination with existing chemotherapeutic regimens, it is not yet approved by NICE, and use has to be agreed case-by-case (see: <http://news.bbc.co.uk/1/hi/england/london/6904342.stm>). As for other cancers where biological agents are proving to be useful, their expense can limit deployment. Most patients with advanced disease will not survive more than 5 years after diagnosis. There is therefore an urgent need to improve survival outcomes in patients with metastasised CRC using affordable interventions, if possible.

Artesunate (Figure 1) is one of the most widely used antimalarial compounds in the world. It was discovered by Chinese scientists in the early 1970s, and since then has proved itself (together with other derivatives in this class of artemisinin compounds, such as artemether and dihydroartemisinin) effective and safe when used in the treatment of tens of millions of adults and children [3-5].

**Figure 1.** Artesunate (artesunic acid). The chemical structure shows an endoperoxide bridge (red) and a 3rd. oxygen (purple) that together making up a trioxolane moiety essential for antimalarial activity.

**O**

**O**

**O**

**O**

**O**

**H**

**H**

**O**

**O**

**O**

**H**

**5**

a

Efferth first showed that artesunate has anti-cancer activity when tested against leukaemia cells [6] and subsequently dozens of cell lines [7]. Highest anti-cancer activity was against leukaemia and CRC cell lines, although this class of compound has activity against a large number of difficult-to-treat unrelated cancers, including ovarian cancers, melanomas and sarcomas (reviewed in [8]).

## Mechanisms of action

The mechanisms of action of artesunate as an antimalarial and its anti-cancer properties are likely to differ (reviewed [13] [8] [14]). Whatever the molecular basis for anti-cancer effects of artesunate, pro-apoptotic [6, 15] and anti-angiogenic properties [16] are observed in diverse experimental models of cancer, including CRC [9].

## Summary

Artesunate is a safe and effective antimalarial that has not yet been examined systematically for its anticancer properties, despite there being a compelling scientific rationale for doing so. At St. George’s, there is world-class expertise in the use of artesunate (all aspects from mechanisms of action [17] [18], up to Phase IV clinical studies with the drug [19] [20] [21]) as well as in the pathophysiology and multidisciplinary management of CRC [22] [23, 24]. In addition, we have developed collaborations with the first group to have defined anti-cancer properties of artemisinins ([7, 8]).

# Study Objectives

The primary objective of the study is to determine the anticancer effect of oral artesunate in colorectal adenocarcinoma defined as the proportion of malignant cells undergoing apoptosis.

Secondary outcome measures are to establish the tolerability of oral artesunate in colorectal cancer and the effects of artesunate on tumour markers and other clinical endpoints.

# Study Design

This will be a Phase I randomised placebo-controlled double-blind trial of artesunate given orally to patients with histologically confirmed CRC who will receive treatment with curative intent. The study will involve 22 patients randomly assigned to receive artesunate or placebo. The overall study duration will be 14 days. An interim efficacy analysis is planned after the first ten patients have completed the study.

A Data Monitoring Committee (DMC) will supervise the study. The primary role of the DMC is to protect the safety of the patients participating in the study by reviewing the safety information. Clear criteria for terminating the study prematurely are given. The DMC is composed of three individuals, an individual with expertise in the conduct of drug trials involving artesunate, a statistician and a colorectal surgeon with a specialist knowledge of the management of colorectal cancer.

# Selection of Patients

## Inclusion criteria

- Aged 21 – 90 years
- With biopsy confirmed single primary site colorectal adenocarcinoma
- With all stages (defined according to conventional criteria, summarised in [1]) that are amenable to surgical treatment and do not require neoadjuvant treatment
- With planned resection
- With written, informed consent

## Exclusion criteria

- Contraindication to use of artesunate due to hypersensitivity
- Pregnancy (of any stage)
- History of hearing or balance problems
- Immunosuppression or concomitant medication known to interact with artesunate (see below)
- Weight < 50 kg or > 100 kg
- Severe anaemia (haemoglobin < 8 g/dl)
- Other planned intervention, apart from standard of care
- Inability to give informed consent
- Inability or unwillingness to take effective contraception in women of child-bearing age
- Chronic kidney disease of NKF D/QOFI stage 3 or above (eGFR <60ml/min)
- Bilirubin > 2x upper limit of normal in the absence of haemolysis, or known chronic liver disease

## Recruitment

Potential subjects will be identified from lists of patients attending the surgical oncology clinic or from lists of patients discussed at the weekly Lower Gastrointestinal Cancer Multidisciplinary Meeting. Patients who have received histological confirmation of their diagnosis and are planned for curative resection, will be recruited by a Surgical or Medical Research Fellow, who has been trained in clinical research to standards of Good Clinical Practice. Patients will be given an information sheet (Appendix 3, May 2010, version 4) regarding the trial and procedures. They will have an opportunity to question the researchers and time to come to a decision about whether or not to take part in the study. There will be no delay in surgery if patients are entered into this study, nor any other change in clinical management, and the 62 day rule will be strictly adhered to.

# Study Medication

## Artesunate and placebo

Artesunate (Arinate® 100mg) and matching placebo tablets are manufactured under Licence according to cGMP by Dafra Pharma (Belgium). Quality Control of study medication is assured by Dafra Pharma in accordance with the apropriate regulatory framework. This will be the only material contribution of Dafra to the trial. **Study medication will be packaged, labelled and certified by B&C CliniPack (Belgium) and will be in pack sizes of 30 x 100 mg.** Study medication will be imported, stored and dispensed by the Pharmacy at St George’s Healthcare NHS Trust.

## Drug dosing

The dose of artesunate for the study will be 200mg od for fourteen days. There are no data on the most appropriate dose of artesunate in cancer in humans. This dose has been chosen by a consensus among experts in the field of artesunate.

The daily dose of artesunate used in combination treatments to treat uncomplicated *Plasmodium falciparum* malaria is 4 mg/kg, given over three days. When given as monotherapy for uncomplicated falciparum malaria the total dose is approximately 20mg/kg, over seven to ten days. The total dose of artesunate for a patient in this study will be between 28 mg/kg and 56 mg/kg, depending on the weight of the subject (ranging between 50-100 kg).

## Packaging and storage conditions

Study medication will be provided in blister packs. One patient box will provide 14 doses, sufficient for the duration of the study. The content of the labelling will be in accordance with local regulatory specifications and requirements.

Arinate® has a shelf life of 3 years if stored at room temperature.

## Drug interactions with artesunate

There are no reports of negative drug interactions with artesunate to date. The manufacturers of artemesinins available in the UK advise against concomitant use with:

- Anti-arrhythmics: procainamide or quinidine
- Antibacterials: macrolides and quinolones
- Antidepressants
- Antifungals: imidazoles and triazoles
- Antipsychotics

Patients who are taking these medications will not be recruited. If such treatment is required on medical grounds, and cannot wait until the end of the study period, the trial medication will be withdrawn and the reason documented by the investigators.

## Pregnancy

Artesunate is teratogenic in animal models and is contraindicated in pregnancy in humans. Pregnant women will not be recruited and subjects will be required to use effective methods of contraception during the study.

## Assessment of medication compliance

An assessment of medication compliance will be made by the investigators at the end of the treatment course based upon verbal answers given to direct questioning and a count of untaken medication. Any unused medication will be returned to the Pharmacy at St George’s Healthcare NHS Trust for disposal in a self-addressed stamped envelope provided to the patient.

# Patient Safety

## Definitions of adverse event and serious adverse event

All events occurring whilst participants are taking the study medication will be recorded on the case record form and managed appropriately in accordance with local and national regulations.

An adverse event (AE) is defined as any untoward medical occurrence in a patient administered a pharmaceutical product and which does not necessarily have to have a causal relationship with this treatment. A priori, efficacy endpoints will not be considered as AEs except if, because of the course or severity or any other features of such events, the investigator, according to his/her best medical judgement, considers these events as exceptional in this medical condition. All AEs will be classified according to the Common Terminology Criteria for Adverse Events v3.0 of the Cancer Therapy Evaluation program.

A serious adverse event (SAE) is any untoward medical occurrence that:

- Results in death or;
- Is life threatening or;
- Requires inpatient hospitalisation or prolongation of existing hospitalisation or;
- Results in persistent or significant disability/incapacity or;
- Is a congenital anomaly/birth event or;
- Is a medically important event

Medical and scientific judgement will be exercised in deciding whether expedited reporting is appropriate in other situations, such as important medical events that may not be immediately life-threatening or result in death or hospitalisation but may jeopardise the patient or may require intervention to prevent one of the other outcomes listed in the definition above.

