## Obligation of the investigator regarding safety reporting

All AEs, regardless of seriousness or relationship to the study medication are to be recorded in the Case Record Form. Whenever possible, symptoms will be grouped as a single syndrome or diagnosis. The investigator will specify the date of onset, intensity, action taken with respect to study medication, corrective treatment/therapy given, outcome and his/her opinion as to whether there is a reasonable possibility that the AE was caused by the study medication.

In the case of a SAE the investigator must immediately:

- Ensure appropriate medical care of the study participant and follow-up until clinical recovery is complete
- Inform, in writing, the DMC including a signed and dated copy of the case record form
- Inform the study Sponsor using the appropriate local form (available at <https://intranet.sgul.ac.uk/admin/research/clinic/index.php>)
- In the case of any SAE brought to the attention of the investigator at any time after the cessation of the study medication and considered by him/her to be caused by the study medication with a reasonable probability, this should be reported to the DMC

In the case of an AE, when knowledge of the identity of the study medication is essential for treating the patient, the code for randomisation will be broken. Wherever possible this should be initiated by the DMC. In the event of an emergency an unblinding procedure may be authorised by the investigator. If the blind is broken, the investigator will document the time, date and reason for code breaking in the case record form.

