# Study Procedures

## Visit schedule

Subjects will be identified and recruited as described above. The case record form will be completed, vital signs documented, an ECG performed and baseline blood samples taken at the time of the first visit, prior to randomisation. Patients will be reviewed in a private room in the surgical outpatient department.

A second review is planned after seven days of study medication. This semi-structured interview will be conducted in person and a blood test will be taken to check for haematological and biochemical parameters. Any subject who experiences any self-reported adverse events will be reviewed in person at the earliest opportunity.

A review is planned at the end of the two week period of study medication. In addition to a clinical review including recording of vital signs, repeat blood samples will be taken and an ECG performed. A further brief review for the purpose of determining any adverse events that may have occurred after the end of the period of treatment with the study drug will be performed during the operative inpatient stay (or at a relevant timepoint in the case of cancellation of surgery). **A final blood sample will be taken approximately 28 days after the date of surgery, at a routine postoperative clinic appointment.**

Participants will be provided with contact details for the investigators. Additional reviews will be arranged, if necessary, at the participants’ request.

It is anticipated that the study medication will be started fifteen days before the scheduled surgery to co-ordinate the end-of treatment study assessment with the pre-operative admission assessment.

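### Five sections define the adverse event window inconsistently, no enquiry is stated after the inpatient review, and post-treatment SAEs reach the DMC only if judged drug-caused

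*Combined protocol and SAP*

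**What the plan says.** All references are to the combined protocol and SAP.

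- **Definitions of adverse event and serious adverse event:** recording is tied to drug intake, in the words "All events occurring whilst participants are taking the study medication will be recorded on the case record form". No end date is given.
- **Obligation of the investigator regarding safety reporting:** the recording duty here reads "All AEs, regardless of seriousness or relationship to the study medication are to be recorded in the Case Record Form". No time limit is given.
- **Same section, SAEs after treatment:** the last item in the list of SAE duties opens "In the case of any SAE brought to the attention of the investigator at any time after the cessation of the study medication". Its condition for reporting is that the event is "considered by him/her to be caused by the study medication with a reasonable probability, this should be reported to the DMC".
- **Laboratory test monitoring:** abnormalities count as adverse events if they develop or worsen in the study period, a term that is not defined.
- **Study Design:** "The overall study duration will be 14 days".
- **Visit schedule:** a brief review takes place during the operative inpatient stay, and its stated aim is "determining any adverse events that may have occurred after the end of the period of treatment with the study drug". If surgery is cancelled, it is done at another suitable time. Appendix 1 also shows a post-treatment review at surgery.
- **Visit schedule, last contact:** "A final blood sample will be taken approximately 28 days after the date of surgery, at a routine postoperative clinic appointment". No adverse event enquiry is mentioned there.
- **Secondary outcome measures - tolerability:** tolerability is compared with placebo, with no time window stated.

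**The concern.** Patients have a bowel resection almost immediately after a course of an investigational drug. Complications are to be expected from the operation itself, so an investigator looking at one patient has little basis for separating a drug contribution from a surgical one. The randomised comparison avoids that judgement, but only if events are collected in the same way in both arms and whatever their presumed cause.

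Two things are at stake. The first is oversight: the Study Design section makes patient safety the DMC's primary role, and the criteria for premature discontinuation let the DMC stop the study on doubt about risk and benefit. If SAEs attributed to surgery are not sent to it, it cannot see whether they cluster in one arm. The second is the tolerability comparison: with no single end of collection, investigators may reasonably stop asking at different times, and the tolerability data will then cover different periods in different patients.

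**Working it through.** The plan states no figure for the length of adverse event collection, so there is none to reproduce. The check is a day count followed by a comparison of sections.

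**Inputs.** Treatment lasts 14 days (Drug dosing). Drug is expected to start 15 days before surgery (Visit schedule). The last contact is about 28 days after surgery (Visit schedule).

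**Day count.**
- End of treatment to surgery: 15 − 14 = about 1 day.
- First dose to last contact: 15 + 28 = about 43 days.
- End of treatment to last contact: 43 − 14 = about 29 days.
- Inpatient review to last contact: 28 − L days, where L is the number of days from surgery to the review. The plan does not fix L. As an assumption only, L = 3 gives 25 days and L = 10 gives 18 days.

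**Where each section puts the end of collection.**
- Definitions: the last dose, about one day before surgery.
- Investigator's obligations, general sentence: no end.
- Laboratory test monitoring: end of the study period. If that means the 14 days in Study Design, it also ends before surgery.
- Study Design: day 14. This cannot be the whole study, because the tissue for the primary endpoint is taken at resection (Data collection; Other histological assessments).
- Visit schedule: at least to the inpatient review, with a further contact about 28 days after surgery for which only a blood sample is specified.

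These cannot all describe one window, and none names a closing date that fits the last contact.

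**The SAE route.** The general duty to inform the DMC of an SAE has no time limit, but a separate item deals with SAEs after cessation and adds a causality condition. If the general duty already covered that period, the separate item would add nothing. The natural reading is therefore that the condition governs after the last dose. With surgery about a day later, it governs essentially all post-operative SAEs. Prolonged hospitalisation is one of the listed SAE criteria, and on the expected schedule a prolonged operative stay can arise only in this period.

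**What a table by arm can show.** There are 11 patients per arm. With no events on placebo, the two-sided Fisher p-value is:
- 4 of 11 on artesunate: 2 × C(11,4)/C(22,4) = 2 × 330/7315 = 0.090.
- 5 of 11 on artesunate: 2 × C(11,5)/C(22,5) = 2 × 462/26334 = 0.035.

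The plan gives no complication rates. For assumed rates of 20% against 40%, 30% against 60%, and 20% against 60%, the power of the two-sided 5% Fisher test, summed over all outcomes with 11 per arm, is about 7%, 16% and 32%. The table is descriptive and would show only a large excess.

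**The case against.** The strongest reply is that the plan already looks beyond treatment. The definitions section does not say that later events go unrecorded, the investigator's duty to record all adverse events has no limit, and a dedicated review covers the time after treatment during the operative stay. This stands. A reader might infer from the definitions section that events are recorded only on drug, that 14 of 43 days (33%) are covered, and that everything after surgery is lost. The documents do not support that: the percentage measures one sentence in isolation, the early surgical period has its own review, and an unstated enquiry at the clinic visit does not prove that events would be missed.

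A reader might also treat artesunate as a known surgical hazard because "anti-angiogenic properties [16] are observed in diverse experimental models of cancer". That statement concerns experimental models. The section on adverse events associated with artesunate lists no bleeding or wound-healing effect, and the point does not depend on one.

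It can further be said that the SAE wording is ambiguous rather than an exclusion, that the case record form pages are not shown and may include a post-operative page, and that 22 patients can show little. Each is fair. But a form page would not reconcile the protocol text, an ambiguous reporting rule still leaves the choice to each investigator, and the DMC's need to see serious events does not depend on statistical power.

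Finally, a longer window has side effects: the planned admission could count as an SAE, and expected post-operative laboratory changes could become adverse events. The fix has to deal with both.

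**Conclusion.** The point holds in a limited form. The sections on the adverse event window conflict and must be reconciled. No end of collection is stated. No enquiry is stated between the inpatient review and the contact about 28 days after surgery, a gap of 28 − L days that cannot be fixed from the documents. The causality condition on SAEs after the last dose means that post-operative SAEs attributed to surgery need not reach the DMC or enter a comparison between arms.

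This rests on the expected schedule of surgery about one day after treatment ends, and on reading the separate SAE item as replacing the general duty after cessation. It does not rest on any assumed drug effect on surgical recovery. The primary endpoint analysis is unaffected. It is a low-cost improvement to safety oversight and to the tolerability comparison, and should be made.

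**What to change.** 1. Replace the differing wording in Study Design, Definitions, Obligation of the investigator, Laboratory test monitoring and Visit schedule with one window: all adverse events and SAEs, regardless of attribution, from first dose to the existing visit about 28 days after surgery.
2. State that adverse events are asked about at that visit.
3. Send every SAE in the window to the DMC, except the planned surgical admission itself.
4. Tabulate post-operative events by arm, labelled as descriptive.
5. In Study Design, give 14 days as the treatment period and state safety follow-up separately. Say whether completing the study (the trigger in Interim analysis) and the study period (in Laboratory test monitoring) mean treatment or follow-up, so that the interim trigger does not move and expected post-operative laboratory changes do not become adverse events by accident.

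The cost is a protocol amendment, more adverse event and SAE reports (mostly surgical), and possibly one case record form page. No new visit is needed.
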